## Abstract

**Background:**

Pancreatic cancer is a devastating disease with less than 5% 5-year survival. Inoperable patients often present with pain. Randomized controlled trial have shown that endoscopic ultrasound-guided celiac plexus neurolysis (EUS-CPN) improves pain control. It is usually performed by injecting bupivacaine followed by absolute alcohol around the celiac axis.

**Study design:**

Single center, randomized, double blind controlled trial of EUS-CPN with and without bupivacaine in patients with inoperable malignancy (pancreatic or other) involving the celiac plexus. The study was approved by research ethics board with approval number of 2022-9969, 21.151 and registered on ClinicalTrials.gov (NCT04951804).

**Discussion:**

We hypothesize that bupivacaine is superfluous and may actually reduce pain control by diluting the neurolytic effect of alcohol. Bupivacaine is also potentially dangerous in that it may produce serious adverse events such as arrythmias and cardiac arrest if inadvertently injected intravascularly.

**Conclusion:**

This randomized trial is designed to assess whether bupivacaine is of any value during EUS-CPN.

**Supplementary Information:**

The online version contains supplementary material available at 10.1186/s13063-023-07487-7.

## Background

Pancreatic cancer is the most devastating of all cancers with a dismal survival rate. Pancreatic cancer is the 3rd most common cause of cancer-related deaths worldwide. The 5-year survival rate of all patients with pancreatic cancer is approximately 5%, and this figure has remained relatively stable over the past 25 years, since most patients present with inoperable disease [1, 2].

Seventy to 80% of patients with pancreatic cancer have abdominal pain at the time of diagnosis, which reduces quality of life and possibly survivability. Adequate pain control is therefore considered an essential component for the care of these patients. In the initial phase, the pain is visceral, but with disease progression, somatic pain may occur, especially due to the peri-pancreatic invasion of neural structures, such as the celiac plexus [3].

The effectiveness of CPN is well established. It is safe, produces significant pain reduction, significantly reduces narcotic requirements, and may even increase survivability [4–6]. Wyse et al. were the first to publish a randomized, sham-controlled trial demonstrating the efficacy of EUS-CPN for pain due to pancreatic cancer and authored the most recent published guidelines on the use of EUS-CPN [4, 7].

Currently, it is standard EUS-CPN practice to inject bupivacaine immediately before injecting absolute alcohol, to theoretically prevent pain during and after the procedure [7]. However, the true value of bupivacaine during neurolysis has never been studied. There are no data showing whether bupivacaine injection has any real influence on intra-procedural, immediate post-procedural, or long-term pain control. The injection of bupivacaine before the alcohol may have no effect, a synergistic effect, or an antagonistic effect, by diluting the alcohol and reducing its neurolytic capacity. Inadvertent intravascular injection of bupivacaine may also cause irreversible cardiac arrythmias and death [8]. In other words, in the worst-case scenario, the injection of bupivacaine may increase procedural risk, with questionable effect in terms of pain reduction.

In our institution, we stopped applying bupivacaine during EUS-CPN approximately 2 years ago, with no obvious difference intra- or post-procedure and a possible reduction in the need for repeat neurolysis—suggesting that neurolysis without bupivacaine may be more effective (unpublished observations).

Therefore, we designed a randomized clinical trial to determine if bupivacaine is of any value during EUS-CPN.

## Methods

### Objectives and design

The primary hypothesis for this study is that bupivacaine injection before neurolysis dilutes the neurolytic effect of alcohol and therefore decreases its analgesic effectiveness. We also believe that bupivacaine injection has no influence on intra- or immediate post-procedural pain.

The primary aim of study is to compare the effectiveness of EUS-CPN with and without bupivacaine. Secondary aims include a comparison of intra- and post-procedural pain, narcotic use, adverse events, and survival between the studied groups.

This is a single-center, randomized, double-blinded, parallel groups, non-inferiority clinical trial to be performed at the endoscopy unit of the Centre Hospitalier de l’Université de Montréal (CHUM) in Québec, Canada.

The SPIRIT reporting guidelines have been used in protocol formulation [9].

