### Sample size calculations

The sample size, estimated in relation to the primary outcome, is based on the detection of a minimum clinical difference of 3 points on the Likert scale between the 2 study groups, with a beta error of 20%, an alpha error of 5%, and a standard deviation of 7. *n* = 2 × 7.8 × (7/3) 2 = 2 × 7.8 × 5.4 = 90 per group.

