### Statistical analysis

Descriptive statistics will assess patient characteristics (demographics, tumor size) and the balancing of randomization. The data will be tested for normality, and the paired Wilcoxon ranked sum test will assess the pain scores. Student’s *t* test will be performed when comparing two means. Fisher’s exact method will be used for proportions comparison. All *p*-values are two-tailed, and values < 0.05 will be considered statistically significant. Subsequent logistic regression modeling will determine the factors that are associated with a better pain outcome.

Kaplan-Meier estimates of the survival curve will be obtained for each treatment group, and statistical comparisons of these will be performed using the log-rank test. The Cox proportional hazards models will be used to study survival while adjusting for potential confounding factors.

Patients who withdraw will be noted and will be noted and they will be excluded from analysis.

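### The trial is labelled non-inferiority, but its hypothesis, sample size and tests are those of a superiority trial and no margin is stated

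*Protocol article*

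**What the plan says.** All references are to the protocol article.

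- **Label.** Objectives and design: "This is a single-center, randomized, double-blinded, parallel groups, non-inferiority clinical trial".
- **Primary hypothesis.** The same section: "bupivacaine injection before neurolysis dilutes the neurolytic effect of alcohol and therefore decreases its analgesic effectiveness". This is a directional claim that alcohol alone is better.
- **Primary aim.** The same section: "The primary aim of study is to compare the effectiveness of EUS-CPN with and without bupivacaine". It mentions neither a margin nor which arm is to be non-inferior to which.
- **Sample size.** Sample size calculations: the number is "based on the detection of a minimum clinical difference of 3 points on the Likert scale between the 2 study groups", with beta 20%, alpha 5% and SD 7, giving 90 per group.
- **Decision rule.** Statistical analysis: Wilcoxon, t and Fisher tests, all two-tailed, where "values < 0.05 will be considered statistically significant".
- **Primary outcome.** Change in Likert pain score from baseline to day 30. Treatment failure is a fall of less than 3 points. Table 2 shows that the scale runs from 0 to 6.

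**The concern.** A non-inferiority trial needs three things that a superiority trial does not: a stated direction, a margin, and a rule that compares a confidence limit with that margin. The article gives the label without any of them. What it does give (a directional hypothesis, a difference to detect, a two-tailed p-value) belongs to a superiority trial.

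The mismatch matters because the Background describes bupivacaine as standard practice and the trial asks whether it has any value. If the comparison is not significant, the label invites the conclusion that alcohol alone is no worse. A difference test cannot support that conclusion. How often the situation would arise when alcohol alone really is worse depends on the SD and on the true deficit, as worked out below.

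**Working it through.** **1. The article's own sample size.** The formula is n per group = 2 × 7.8 × (SD/difference)². The multiplier 7.8 is approximately (1.96 + 0.84)² = 7.84, that is, two-sided 5% and 80% power. With the printed rounded values, 2 × 7.8 × 5.4 = 84.2; with (7/3)² unrounded it is 84.9; with exact normal quantiles it is 85.5, so 86. The printed 90 is not reproduced, but that is a separate matter. I use 90 per group below because it is the stated target.

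**2. Does n distinguish the two designs?** No. Non-inferiority with a 3-point margin, zero true difference, one-sided 2.5% and 80% power uses the same formula and also gives 86. The evidence for superiority is the wording and the tests.

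**3. Can the 3 points serve as an implicit margin?** Three facts speak against it:
- they are described as a difference to detect;
- they are half of the 0–6 range (3/6);
- they equal the within-patient fall that separates success from treatment failure, so such a margin would tolerate an average loss as large as a whole treatment success.

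**4. How often p ≥ 0.05 occurs when alcohol alone is truly worse by d.** SE = SD × √(2/n). P(p ≥ 0.05) is 1 minus the power of the two-sided t test with 2n − 2 degrees of freedom (non-central t). The normal approximation is 1 − Φ(d/SE − 1.96), ignoring the negligible opposite tail, and agrees within about one percentage point for d = 1. Example: SD 2, n = 90 gives SE = 2 × √(2/90) = 0.298; for d = 1, 1 − Φ(3.354 − 1.96) = 1 − Φ(1.394) = 0.08.

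The SDs of 2, 2.5 and 3 are assumptions. The article states 7, but a 0–6 score cannot have an SD much above 3 (half its range), and its change, running from −6 to +6, cannot have one much above 6.

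| SD | SE (90 per group) | P(p ≥ 0.05), d = 0.5 | P(p ≥ 0.05), d = 1 |
|---|---|---|---|
| 2 | 0.298 | 61% | 8% |
| 2.5 | 0.373 | 73% | 24% |
| 3 | 0.447 | 80% | 40% |
| 7 (stated) | 1.043 | 92% | 84% |

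**5. What a real margin would need.** Power at zero true difference with a 95% CI rule is about Φ(margin/SE − 1.96); the table uses the t version. The 1-point margin is for illustration only. The second column is included because the Duration section gives the requirement as 90 patients, which could be read as the total.

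| SD | 90 per group | 45 per group |
|---|---|---|
| 2 | 92% | 65% |
| 2.5 | 76% | 47% |
| 7 (stated) | 16% | 10% |

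By the normal formula, 80% power at a 1-point margin needs 2 × (SD × 2.80)²: 63 per group at SD 2, 99 at SD 2.5 and 770 at SD 7.

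**The case against.** The strongest reply is that this is one stray word. It does not appear in the abstract's design statement, in the conclusion or in the primary aim. Everything else in the article already describes a superiority trial, so no test and no sample size is wrong on this account. That is fair, and it is why the simplest remedy is a change of wording.

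Several stronger readings are tempting, and the document does not support them:

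- **That the trial cannot show non-inferiority at all.** A two-tailed p below 0.05 in favour of alcohol alone, which is the hypothesised result, would show superiority and therefore also non-inferiority at any margin. Only a non-significant result is barred.
- **That the investigators plan to read p ≥ 0.05 as non-inferiority.** The article never says so. The label, with no other rule beside it, merely leaves this open.
- **That no margin exists.** The article is condensed, and the full protocol and analysis plan are not shown. What can be said is that none is stated here. The contradiction remains, because the article itself gives the hypothesis, the sample size and the decision rule.
- **That the sample size proves superiority.** A 3-point margin would give the same n.
- **That the statement "We also believe that bupivacaine injection has no influence on intra- or immediate post-procedural pain" is a planned equivalence claim.** It is worded as a belief, and the matching secondary aim is only a comparison.
- **That the registry entry carries the same error.** It is not available, so nothing can be said about it.

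**Conclusion.** The point holds in a limited form. The label contradicts the hypothesis, the sample-size rationale and the tests in the same article. A significant result favouring alcohol alone would be sound under either name. A non-significant result could not support non-inferiority, and the document does not rule out that reading.

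The size of the risk depends on the SD. At 90 per group and assumed SDs of 2 to 3, a true 1-point deficit would be missed 8% to 40% of the time and a 0.5-point deficit 61% to 80%. At the stated SD of 7 the figures are 84% and 92%, but that SD is not credible on this scale. No single figure should be quoted without its SD. Although the correction is mainly one of wording, it is needed because the framing governs what the primary result may claim.

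**What to change.** **Preferred.** Delete the non-inferiority label and describe the trial as two-sided superiority. Report the day-30 between-group difference in Likert change with its 95% CI, and state that p ≥ 0.05 will not be read as equivalence or non-inferiority. This changes no test, sample size or procedure; it costs an amendment to the wording. The Trial status section reports 36 patients already recruited, so it should be done before unblinding.

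**If the sponsor keeps the label.** Before unblinding, state that alcohol alone is to be shown non-inferior to alcohol with bupivacaine (if that is the intended direction). Justify a margin well below 3 points on the day-30 difference, require the 95% CI limit to lie inside it, and restate the power for that margin with a defensible SD. Whether 90 is per group or in total must be settled first. On the figures above, a 1-point margin reaches 80% power with 90 per group at SD 2 but not at 2.5, and with 45 per group at neither, so this route may require more patients.

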### Study population

All patients referred for EUS for suspected pancreatic malignancy or for neurolysis for pain due to proven pancreatic malignancy are eligible. The study will be presented to them by a single research assistant, who will also obtain study consent before the procedure. Patients will be randomized if they meet all inclusion criteria and have no exclusion criteria presented in Table 1.

**Table 1 Tab1:** Inclusion and exclusion criteria for the study

**Inclusion criteria**	1. Malignant-appearing pancreatic mass, or proven pancreatic cancer involving the pancreatic genu, body, or tail on imaging done before the endosonography 2. Any level of abdominal or back pain considered to be potentially related to the mass: a. New onset pain (< 3 months) b. Constant c. Centrally located d. With or without irradiation to the back e. No obvious other source of pain 3. No possibility of immediate surgical management. (Based on EUS evidence of venous involvement ≤ 1 cm from portal confluence and/or arterial involvement of the celiac axis or the splenic artery ≤ 1 cm from the bifurcation of the celiac axis, and/or evidence of liver metastases) 4. Signed, informed consent 5. Celiac axis accessible for *bilateral* neurolysis at EUS
**Exclusion criteria**	1. Allergy to bupivacaine 2. Tumors amenable for curative resection 3. Significant coagulopathy (platelets < 50000 µ/L, INR > 1.4, uninterrupted use of oral anticoagulants at therapeutic dosage [except for antiplatelet agents] 4. Patients with concurrent sepsis 5. Previous EUS CPN

### Sample size calculations

The sample size, estimated in relation to the primary outcome, is based on the detection of a minimum clinical difference of 3 points on the Likert scale between the 2 study groups, with a beta error of 20%, an alpha error of 5%, and a standard deviation of 7. *n* = 2 × 7.8 × (7/3) 2 = 2 × 7.8 × 5.4 = 90 per group.

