**Fig. 1 Fig1:**
[figure not shown]
Schedule of enrolment interventions and assessments

Immediate post-procedural surveillance:Likert pain scores pre-procedure (T0) and 30 min after arriving in recovery (T30) and then every 30 min until dischargeOpioid use in the last 3 days before the procedureVital signs pre-procedure (T0), immediately before and after neurolysis, and at 30 min after arriving in recovery (T30), and then every 30 min until dischargeRequirements for analgesia during the recovery period

Post-discharge surveillance:

Telephone interviews by a single research assistant on days 3, 7, 30, 60, 90, and 120* for:7-point Likert scale for pain (Table 2)Global rating scale of change (GRSC) (Table 2)Any adverse events (diarrhea, fever, dizziness, leg weakness)Hospital visitsNarcotic use.

**Table 2 Tab2:** Likert pain scale and GRSC

**7-point Likert scale for pain**	0 No discomfort at all 1 Minor discomfort 2 Mild discomfort 3 Moderate discomfort 4 Moderately severe discomfort 5 Severe discomfort 6 Very severe discomfort
**Global rating scale of change (GRSC)**	0 No improvement at all 1 Minor improvement 2 Mild improvement 3 Moderate amount of improvement 4 Quite a bit of improvement 5 A lot of improvement 6 Great improvement

*Days 3 and 7: ± 2 days; days 30, 60, 90, and 120: ± 4 days

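### The sample-size line rests on an SD that the 0–6 pain scale cannot produce, and its printed product is not 90; both errors are conservative, but 90 per group is left without a valid justification

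*Protocol article*

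**What the plan says.** The Protocol article, Sample size calculations, bases the trial's size on "a minimum clinical difference of 3 points on the Likert scale between the 2 study groups". Its other inputs are 20% beta, 5% alpha and an SD of 7. It puts these into the usual two-mean formula and prints "2 × 7.8 × 5.4 = 90 per group". The paragraph mentions no attrition allowance, no correction for a rank test and no rounding rule.

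The scale is defined in Table 2 under Patient follow-up. It has seven categories scored 0 to 6, beginning "0 No discomfort at all 1 Minor discomfort 2 Mild discomfort". The Primary outcome section compares the groups on the change in this score from before the procedure to day 30. Statistical analysis sets two-sided testing at the 5% level: "values are two-tailed, and values < 0.05 will be considered statistically significant".

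The Duration section gives the requirement as 90 patients, without saying whether that is per group or in total. It applies a 50% refusal and dropout rate there, to the recruitment time only.

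**The concern.** Two things on this line do not fit.

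- **The SD.** The paragraph uses "a standard deviation of 7" for a scale whose full width is 6 points. The formula depends on the square of the SD, so an impossible value makes the resulting n uninformative.
- **The product.** The three printed factors do not multiply to the printed result.

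This paragraph is the only justification given for the target size. If its inputs cannot describe the endpoint, the stated pairing of a 3-point difference with 20% beta does not describe the trial. A reader of the results, above all of a null result, would then judge them against the wrong detectable difference.

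**Working it through.** **Inputs.** Difference 3 points, SD 7, alpha 5%, beta 20%, stated n of 90 per group (Sample size calculations); two-sided testing (Statistical analysis); 1:1 allocation (Randomization and blinding); score range 0 to 6 (Table 2); endpoint the change from T0 to day 30 (Primary outcome).

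**1. The plan's own figure.** Formula: n per group = 2 × (z for alpha + z for beta)² × (SD/difference)².

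- Factors as printed: 2 × 7.8 × 5.4 = 84.24.
- Keeping (7/3)² = 5.444: 2 × 7.8 × 5.444 = 84.93.
- Full precision: 2 × 7.849 × 5.444 = 85.47, so 86.
- Two-sample t-test: 86.4, so 87.
- One-sided 5%: 68.
- Non-inferiority with a margin of 3: 86 at one-sided 2.5%, 68 at one-sided 5%.

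None of these gives 90. The printed result exceeds the printed product by 5.76 (6.8% of 84.24) and the full formula by 4. An allowance could lead to about 90, such as 5% attrition (85/0.95 = 89.5, so 90) or a rank-test efficiency of 0.955 (85.47/0.955 = 89.5), but the paragraph states neither.

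**2. The largest SD the scale allows.** A variable confined to an interval has an SD of at most half the interval's width.

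- Score, 0 to 6: at most 3 (3.02 for a sample SD with n = 90).
- Change, −6 to +6: at most 6 (6.03 for a sample SD with n = 90).
- Change if every patient scores at least 1 at T0, so −6 to +5: at most 5.5.

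These bounds are reached only if half the patients sit at each extreme. An SD of 7 is above all of them.

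**3. Power for 3 points, two-sided 5%.**

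| SD | Power at 90 per group (normal / t-test) | n per group for 80% power (normal / t-test) |
|---|---|---|
| 7 (as stated) | 82.0% / 81.6% | 86 / 87 |
| 6 (upper bound for a change) | 91.8% / 91.6% | 63 / 64 |
| 3 (assumed) | above 99.9% | 16 / 17 |
| 2 (assumed) | above 99.9% | 7 / 9 |

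Beta at 90 per group is thus about 18% at the stated SD and about 8% or less at any attainable SD. The document gives no attainable SD, so the last two rows are illustrations.

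**4. Difference detectable with 80% power (t-test).** With 90 evaluable per group it is 0.42 × SD: 0.84 points at SD 2 and 1.26 points at SD 3.

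**5. If 90 is the total.** With 45 per group the detectable difference is about 0.60 × SD. Power for 3 points is then about 52–53% at SD 7, 65–66% at SD 6 and 99.7% at SD 3.

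**The case against.** The strongest reply is that nothing is lost. With the plan's own inputs, 90 per group exceeds the 84 to 87 required and gives beta of about 18%, inside the 20% target. Any attainable SD raises power further. A condensed article may also leave out a small round-up: 85.5, 86 and 87 all become 90 to the nearest ten, and a 5% allowance gets there too.

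Most of this stands. A reader might infer from the false product and the impossible SD that 90 per group misses its stated beta, or that the trial is underpowered. The documents do not support that, because both errors push n upward. The arithmetic slip alone is minor.

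What does not stand is that the line can be left as it is. An unprinted round-up may explain the 90, but it does not make the equation true. Condensation does not explain the SD either, because the article prints the input and the value is impossible on its own scale. The value 7 does match the number of scale categories, and one might conclude that this is where it came from. The documents do not say so.

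A further objection is that nothing in the document supports powering the trial for less than the 3 points it calls the minimum clinical difference. That is fair. The detectable difference in the working describes what 90 per group can show; it is not proposed as a new target.

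**Conclusion.** The sample-size line is wrong as written. The SD of 7 exceeds the maximum of about 3 for a score and about 6 for the 30-day change, so the stated inputs do not justify 90 per group and the stated 20% beta does not describe the trial. The printed product is 84.24 (86 by the full formula, 87 by t-test), with no stated step to 90.

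Both errors are conservative, so this is a faulty justification and not a power shortfall at 90 per group. That conclusion assumes a two-sided 5% comparison of mean change, 90 patients per group evaluable at day 30, and 90 meaning per group. The last assumption is not secure, because the Duration section speaks only of 90 patients.

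The point should be fixed, but it does not threaten the design. Nearly all of its weight lies in the SD and little in 84 against 90.

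**What to change.** Rewrite the Sample size calculations paragraph, without raising enrolment:

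1. Correct the product (84, or 86 from the full formula) and state any rounding or allowance that leads to 90.
2. Replace the SD of 7 with an SD of the T0-to-day-30 change that a 0–6 scale can have, and give its source.
3. At that SD, restate the power for 3 points and the difference detectable with 80% power: 0.42 × SD with 90 evaluable per group, for example 0.84 points if the SD is assumed to be 2 and 1.26 if 3.
4. Reconcile 90 per group with the 90 patients in the Duration section. If 90 is the total, the detectable difference is about 0.60 × SD, and the restated figures must use 45 per group.

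The cost is one rewritten paragraph, a clarification in Duration and the search for a sourced SD. Trial status reports 36 patients recruited with recruitment continuing, so the correction can be made before analysis.
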